## Abstract

**Introduction:**

Beyond mood abnormalities, bipolar disorder (BD) includes cognitive impairments that worsen psychosocial functioning and quality of life. These deficits are especially severe in older adults with BD (OABD), a condition expected to represent most individuals with BD in the upcoming years. Restoring the psychosocial functioning of this population will thus soon represent a public health priority. To help tackle the problem, the Bipolar and Depressive Disorders Unit at the Hospital Clínic of Barcelona has recently adapted its Functional Remediation (FR) program to that population, calling it FROA-BD. However, while scarce previous studies localize the neural mechanisms of cognitive remediation interventions in the dorsal prefrontal cortex, the specific mechanisms are seldom unknown. In the present project, we will investigate the neural correlates of FR-OABD to understand its mechanisms better and inform for potential optimization. The aim is to investigate the brain features and changes associated with FROA-BD efficacy.

**Methods:**

Thirty-two individuals with OABD in full or partial remission will undergo a magnetic resonance imaging (MRI) session before receiving FR-OABD. After completing the FR-OABD intervention, they will undergo another MRI session. The MRI sessions will include structural, diffusion-weighted imaging (DWI), functional MRI (fMRI) with working memory (n-back) and verbal learning tasks, and frontal spectroscopy. We will correlate the pre-post change in dorsolateral and dorsomedial prefrontal cortices activation during the n-back task with the change in psychosocial functioning [measured with the Functioning Assessment Short Test (FAST)]. We will also conduct exploratory whole-brain correlation analyses between baseline or pre-post changes in MRI data and other clinical and cognitive outcomes to provide more insights into the mechanisms and explore potential brain markers that may predict a better treatment response. We will also conduct separate analyses by sex.

**Discussion:**

The results of this study may provide insights into how FROA-BD and other cognitive remediations modulate brain function and thus could optimize these interventions.

## Introduction

1

Bipolar disorder (BD) is a chronic mental illness characterized by the presence of manic/hypomanic and depressive episodes alternated with partial or total euthymic periods. This disease frequently presents cognitive deficits mainly affecting attention, executive function, memory, and processing speed (1–3). Unfortunately, these cognitive deficits result in functional impairment and an overall decrease in quality of life, issues that are usually not adequately addressed by traditional pharmacological treatments (4).

In recent years, cognitive impairment has emerged as a key treatment priority in BD. Cognitive Remediation (CR) has shown consistent cognitive benefits in BD (5) with improvements in several cognitive domains, especially attention, verbal memory, and executive functions (6, 7). In fact, it has also been found that cognitive improvements contribute to functional improvement, demonstrating a translation of the therapeutic benefits into the patients’ daily life (8). However, most CR interventions for BD are designed for younger people, overlooking the specific and relevant characteristics of Older Adults with Bipolar Disorder (OABD). According to the latest definition of the International Society for Bipolar Disorders (ISBD) OABD Task Force, OABD is defined as people with BD older than 50 years of age (9). In recent years, special emphasis has been placed on considering OABD as a particular subgroup of the population, since it has been reported that they exhibit specific characteristics, such as a different clinical profile, lower functioning, and the presence of higher rates of somatic comorbidities compared to younger patients (10–12). These findings reinforce the idea of developing and applying specific clinical and treatment strategies adapted for this group of patients.

OABD is considered a vulnerable population to cognitive impairment (13). A recent metanalysis has demonstrated that OABD exhibit significantly worse performance in almost all cognitive domains, especially in the memory domain, but also in attention, working memory, executive functions, and processing speed, compared to healthy controls (14). Impairments in different cognitive domains have also been associated with poorer psychosocial functioning in OABD (15–17). Regardless, the relevance of functional decline, cognitive impairment and reduced quality of life emphasizes the importance of developing and optimizing therapeutic strategies aimed at remediating cognition and functioning in OABD.

However, most interventions that have demonstrated effectiveness in improving cognitive performance have the inconvenience that, on the one hand, are designed for older adults with different psychiatric diagnoses or, on the other hand, are tailored for BD without addressing this age range specifically. This limitation restricts the effectiveness and treatment response in these patients. To maximize therapeutic benefits for this age group, it is crucial to develop interventions tailored to their specific needs (18). Given the scarce evidence of treatments aimed at improving or enhancing cognitive function in OABD, the original “Functional Remediation” (FR) cognitive program for BD (19) was recently adapted to the specific characteristics of OABD, thus creating the FROA-BD program (20). The efficacy of the original FR program was tested in a randomized controlled trial (RCT) that showed that it improved psychosocial functioning (19) and its effects were maintained over time (21). FR also showed to improve verbal memory in those participants showing significant cognitive impairment (22) and was also effective for patients with subsyndromal symptoms (23) as well as for patients with bipolar II type (24). Therefore, the FROA-BD intervention introduces the novelty of attempting to fill this gap in treatment options for this patient group. The FROA-BD focuses on improving cognitive performance, functionality, and quality of life, but also addresses emotion management, social skills, autonomy, strategies for daily living, healthy lifestyle habits, and training in digital competencies.

Understanding the neural correlates of cognitive impairment and cognitive remediation is crucial, as it provides insights into the brain mechanisms underlying cognitive processes and facilitates targeted interventions to enhance cognitive function. In studies investigating the neuronal basis of cognitive impairment in BD, regarding structural brain abnormalities, a greater left dorsomedial prefrontal thickness and a lower cerebral white matter (WM) volume have been associated with cognitive impairment (25). In addition, the most consistent findings regarding neural correlates for cognitive impairment also suggest a failure to activate task-relevant prefrontal regions and to deactivate the default mode network (25, 26). The ISBD Targeting Cognition Task Force recommended using neuroimaging in intervention trials to optimize cognitive remediation (27). According to these recommendations, we need to include task-related functional Magnetic Resonance Imaging (fMRI) assessments given that they allow us to identify changes in cognition-relevant function and structure. Moreover, given the paucity of structural neuroimaging intervention studies further studies are needed to clarify the value of these techniques as biomarkers for treatments targeting cognition. In recent years, some interesting studies have investigated brain effects of similar cognitive remediation (CR) programs using Magnetic Resonance Imaging (MRI) and whether baseline MRI can predict improvement in cognition after receiving CR. However, results are still limited, and the studies only have investigated younger patients. One study, which combined participants with BD and depression, found a correlation between improvement in working memory and verbal memory and activation in prefrontal, parietal, and hippocampal regions during n-back working memory and verbal memory tasks (28). A more recent study focused on BD found that improvement in executive functions correlated with dorsolateral prefrontal cortex activation during the n-back working memory task (29). Furthermore, both baseline hypoactivation and reduced dorsolateral prefrontal cortical thickness predicted improved executive functions after 10 weeks of CR intervention (29–31). In this sense, it has been suggested that the association between task difficulty and dorsolateral prefrontal response seems to be based on a bell-shaped load-response curve (25). According to this integrative model, patients show dorsolateral prefrontal hyperactivation when task performance remains at an average difficulty level. In contrast, dorsolateral prefrontal hypoactivation is observed when difficulty decreases compared to controls. As mentioned before, OABD is a population who has received less research, so no consistent findings have been detected in studies investigating neural substrates implicated in cognitive impairment (32) and no studies have examined the neural changes in response to cognitive remediation.

Consequently, there is a lack of a validated theoretical framework for the underlying neurobiological mechanisms of cognitive improvement and cognitive remediation in OABD. The neural mechanisms of cognitive remediation therapies constitute novel strategies to optimize these interventions (32). Neuroimaging will likely reveal neurocircuit-based biomarkers that may inform key general or individual steps to increase the efficacy or personalization of FROA-BD.

Thus, the overarching aim of this study is to investigate the functional brain correlates of this intervention.

### Hypotheses

1.1

The main hypothesis of this study is that, after completing the FROA-BD program, patients will show a correlation between the changes in their dorsolateral or dorsomedial prefrontal cortex activation during a working memory task (compared to baseline) and improved psychosocial functioning.

The secondary, explorative hypotheses are that there exist correlations between changes in other MRI-derived brain signals and cognition and psychosocial improvements and between baseline MRI-derived brain signals and cognition and psychosocial improvements. Based on the above studies finding neural correlates of cognition remediation in BD, we hypothesize that the correlations will involve structural MRI and task-based fMRI. However, due to the study’s novelty, we do not have clear hypotheses about their specific brain locations. That said, previous research on patients with psychotic and bipolar disorders indicates increased cortical thickness in the frontal and parietal cortices at baseline, correlating with enhanced cognitive improvements following CR (30, 31, 33, 34). Thus, we may tentatively hypothesize that increased cortical thickness in these regions will predict significant improvements in cognitive function after FROA-BD.

Finally, the study also hypothesizes that there may be potential differences depending on sex.

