### Objectives

1.2

The main objective is to correlate the pre-post changes in the activation of the dorsolateral and dorsomedial prefrontal cortices during the working memory n-back task (2-back vs. baseline) and pre-post changes in psychosocial functioning assessed with the Functioning Assessment Short Test (FAST).

Secondary, explorative objectives are to correlate (a) pre-post changes in MRI data with pre-post changes in cognition and psychosocial functioning outcomes; and (b) baseline MRI data with pre-post changes in cognition and psychosocial functioning outcomes. For the secondary objectives, we plan to conduct comprehensive whole-brain correlation analyses (corrected for multiple testing) and use several MRI modalities (regional tissue volume, cortical thickness, and surface area; fractional anisotropy and diffusivity measures, activation during the working memory n-back task and a verbal memory task; and frontal spectroscopy).

Finally, we will repeat all the analyses on those results that reach statistical significance according to sex to explore potential differences depending on sex.

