### Sample size estimation

2.2

We aim to include 28 participants because previous studies with 23–28 participants found effects (29–31). In addition, with this sample size, we would have ~80% power to detect moderate correlations (r 0.56) after correcting for multiple testing (correlations in three ROIs: left dorsolateral, bilateral dorsomedial, and right dorsolateral prefrontal cortices). Note that this sample size does not include those patients who, even if consenting to participate, leave the study before finishing the baseline assessment and MRI acquisition.

As we anticipate the possibility of participant attrition during the follow-up, we plan to enroll 32 participants (i.e., ~15% more) to counteract the potential dropouts.

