### Data analysis

2.7

The primary outcome will be the correlation between pre-post changes in the activation of the dorsolateral and dorsomedial prefrontal cortex during the working memory n-back task (2-back vs. baseline) and pre-post changes in psychosocial functioning assessed with the Functioning Assessment Short Test (FAST) (63). Specifically, we will conduct three correlations: one for the left dorsolateral, one for the bilateral dorsomedial, and one for the right dorsolateral prefrontal cortex. We will use a permutation test to correct for multiple testing (three correlation tests).

For the secondary analyses, we will conduct two kinds of correlations: (a) pre-post changes in MRI data with pre-post changes in cognition and psychosocial functioning outcomes, and (b) baseline MRI data with pre-post changes in cognition and psychosocial functioning outcomes. We will include as covariates the variables from age, sex, bipolar disorder type, medication (use of lithium, antiepileptics, antidepressants, and antipsychotics), illness history (duration of the illness and number of episodes), or educational level that show statistically significant associations with the MRI signal or the cognition/functioning outcome; in case that several variables show statistically significant associations, we will select those still showing statistical significance in multiple regression. We will report results for structural MRI analyses using both familywise error rate (FWER) < 0.05 based on conservative permutation tests (64) and threshold-free cluster enhancement (TFCE) (65) and uncorrected *p* < 0.001 (at the exploratory level). For spectroscopy, we will use linear models. Finally, for fMRI analyses, a paired t-test will be conducted on single-subject contrast to examine temporal changes in activation, employing the Nilearn toolbox. We will break down and localize clusters using SDM ‘imgcalc’ tool (66).

We will also repeat all the analyses on those results that reach statistical significance according to sex to explore potential differences.

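### Baseline frontal and parietal thickness is tentatively named as a predictor but gets only whole-brain tests, where a regional correlation of 0.56 would usually miss the corrected threshold

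*Protocol article*

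**What the plan says.** Section 1.1 (Hypotheses) says of the secondary questions that "we do not have clear hypotheses about their specific brain locations". It then qualifies this. Citing earlier work on frontal and parietal cortex, it states that "we may tentatively hypothesize that increased cortical thickness in these regions will predict significant improvements in cognitive function after FROA-BD".

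Section 1.2 (Objectives) lists baseline MRI as a predictor of change as secondary objective (b). For the secondary objectives, "we plan to conduct comprehensive whole-brain correlation analyses (corrected for multiple testing"). Section 2.7 (Data analysis) reports structural results at two levels: family-wise error below 0.05 by permutation with TFCE, and uncorrected p < 0.001, labelled exploratory.

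Regions of interest (ROIs) appear only in the primary analysis, which correlates change in 2-back activation with change in FAST: "We will use a permutation test to correct for multiple testing (three correlation tests"). The power statement in section 2.2 belongs to that analysis: "we would have ~80% power to detect moderate correlations (r 0.56) after correcting for multiple testing", specified as "correlations in three ROIs: left dorsolateral, bilateral dorsomedial, and right dorsolateral prefrontal cortices".

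The Introduction reports from earlier studies that "both baseline hypoactivation and reduced dorsolateral prefrontal cortical thickness predicted improved executive functions after 10 weeks of CR intervention". The Discussion repeats that lower baseline dorsolateral thickness went with greater benefit.

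**The concern.** One secondary hypothesis names where to look, but it is tested as if the location were unknown. A whole-brain correction pays for every location searched. With about 28 patients that price is high, and an effect of the size the study can detect in a single region may not survive it. Baseline prediction is one of two secondary objectives, and the Discussion hopes that baseline MRI could forecast individual response. A null corrected map would say little about frontal or parietal thickness, although it could be read as evidence against them.

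The direction is also unsettled. Section 1.1 predicts that greater thickness goes with improvement. The Introduction and Discussion describe lower dorsolateral thickness as predictive, and reference 30 is cited for both directions.

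**Working it through.** **Inputs.** Section 2.2: "We aim to include 28 participants because previous studies with 23–28 participants found effects", with 32 enrolled to allow for dropout; target r = 0.56; power about 80%; three tests. The article gives neither alpha nor sidedness, so 0.05 two-sided is assumed. It also gives no parcel count and no per-location p equivalent to the family-wise threshold, so ranges are shown. Covariates are ignored.

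**Formula.** Fisher z: power = Φ(√(n − 3) · atanh(r) − z₁₋α/₂). Here √25 · atanh(0.56) = 5 × 0.6328 = 3.164. Each result was checked by simulating the t-test for r on bivariate normal data (200,000 draws).

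**The plan's own figure.** α = 0.05/3 gives z = 2.394 and Φ(3.164 − 2.394) = Φ(0.770) = 77.9%; simulation gives 79.2%. The stated figure of about 80% is reproduced.

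**The same correlation at whole-brain thresholds, n = 28**

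| Threshold | Fisher z | Simulated | Observed \|r\| needed |
|---|---|---|---|
| Uncorrected p < 0.001 (planned) | 45% | 44% | 0.59 |
| 0.05/34 (assumed parcels) | 49% | 49% | 0.57 |
| 0.05/68 (assumed parcels) | 42% | 40% | 0.60 |
| 0.05/148 (assumed parcels) | 34% | 31% | 0.63 |
| 1e-4 per location (assumed) | 23% | 20% | 0.67 |
| 1e-5 per location (assumed) | 11% | 8% | 0.73 |
| 1e-6 per location (assumed) | 4% | 2% | 0.78 |

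If all 32 patients completed, simulated power would be 54% at p < 0.001, 50% over 68 parcels and 12% at 1e-5.

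**TFCE.** A per-location cut-off does not describe TFCE, so it was simulated directly: n = 28, a smooth 100 × 100 field (smoothing SD 3 pixels), thresholds from 300 null maps, and 200 runs for each region radius of 3, 6, 10 and 15 pixels.

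- Regional mean correlates at 0.56 (the quantity an ROI test uses): TFCE at family-wise 0.05 detected it in 11%, 17.5%, 21% and 16% of runs. At uncorrected p < 0.001, some location in the region passed in 50–60% of runs.
- Every location in the region correlates at 0.56: TFCE detected it in 27.5%, 66%, 96.5% and 98.5% of runs.

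**A small regional family instead.** Two tests (α = 0.025, z = 2.241): Φ(0.923) = 82%. Four (z = 2.498): Φ(0.666) = 75%. Five (z = 2.576): Φ(0.588) = 72%. Six (z = 2.638): Φ(0.526) = 70%.

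**The case against.** The secondary aims are called explorative throughout and no power is claimed for them. The 0.56 target belongs to the primary ROIs. The sentence about location is fair hedging: it denies clear hypotheses, cites novelty, and offers the thickness idea only tentatively. Earlier remediation studies were in younger patients and disagree on sign. All of this stands, and it means that the article neither misstates its power nor flatly contradicts itself.

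It also stands that the planned p < 0.001 level gives the effect about an even chance of appearing, and that TFCE could do well if the effect were strong over a broad area. The low figures apply to the corrected level and to a regional-mean effect. The p < 0.001 level has no family-wise control, however, so a hit there cannot confirm a hypothesis.

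A reader might infer that baseline dorsolateral activation is another named hypothesis denied a regional test. The documents do not support that. Section 1.1 expects task-fMRI correlations in general but names no place for them; the dorsolateral activation result appears only as earlier evidence in the Introduction and Discussion.

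**Conclusion.** The point holds as a cheap improvement to the analysis of one tentative hypothesis. For baseline frontal and parietal thickness, the whole-brain search lowers power for a regional-mean correlation of 0.56 from about 79% in a three-ROI test to about 40% over 68 parcels, 2–23% at per-location thresholds of 1e-4 to 1e-6, or 11–21% with TFCE. At the uncorrected level it is about half.

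These figures assume 28 completers, two-sided 0.05, no covariates, and parcel counts, thresholds and a spatial pattern that the article does not give. If the correlation reached 0.56 at every location of a broad region, TFCE would find it in 66–98% of runs and the loss would be small or absent. It would therefore be too strong to say that the effect would be missed whatever its shape, or that the sample-size statement is wrong.

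**What to change.** In sections 1.1, 1.2 and 2.7, prespecify a small regional family for objective (b):

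- **Predictors:** mean baseline frontal thickness and mean baseline parietal thickness. Optionally add mean dorsolateral thickness and baseline 2-back activation in the existing left and right dorsolateral ROIs, labelled as motivated by the earlier findings in the Introduction and Discussion rather than by a hypothesis in section 1.1.
- **Outcome:** one named cognitive change score that is repeated after treatment. The SCIP total is a candidate, since section 2.3 includes its alternative form at the second visit. A second outcome would double the family.
- **Test:** two-sided, with permutation correction over the family.
- **Whole-brain maps:** keep both thresholds as planned, as exploration.

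Reword the location sentence so that it separates the regional hypothesis from the open search, and reconcile the direction given in section 1.1 with that in the Introduction and Discussion. Until that is done, two-sided testing is needed.

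The cost is a few lines of text and a few more formal secondary tests on images already planned. Power for r = 0.56 is about 82% with the two core tests and 72% with all five.

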### Objectives

1.2

The main objective is to correlate the pre-post changes in the activation of the dorsolateral and dorsomedial prefrontal cortices during the working memory n-back task (2-back vs. baseline) and pre-post changes in psychosocial functioning assessed with the Functioning Assessment Short Test (FAST).

Secondary, explorative objectives are to correlate (a) pre-post changes in MRI data with pre-post changes in cognition and psychosocial functioning outcomes; and (b) baseline MRI data with pre-post changes in cognition and psychosocial functioning outcomes. For the secondary objectives, we plan to conduct comprehensive whole-brain correlation analyses (corrected for multiple testing) and use several MRI modalities (regional tissue volume, cortical thickness, and surface area; fractional anisotropy and diffusivity measures, activation during the working memory n-back task and a verbal memory task; and frontal spectroscopy).

Finally, we will repeat all the analyses on those results that reach statistical significance according to sex to explore potential differences depending on sex.

